### Measures

2.5

Survey-Study 1: Table 1 provides the overview of the study measures. The primary outcome measures are sleep disturbances (insomnia; sleep onset latency (SOL); awakenings after sleep onset (WASO) = disrupted sleep continuity). Secondary outcomes are psychological ill-being and well-being, including depression, anxiety, stress, coping strategies, emotion regulation, concentration, social activity, strengths and difficulties, and mental toughness.

Intervention-Study 2: Table 2 provides the overview of the study measures. Primary outcomes are change in sleep disturbances (insomnia; disrupted sleep continuity). Secondary outcomes are psychological ill-being and well-being, including the dimensions metioned above, and additionally: Sleep-related cognitions, experiential avoidance, and mindfulness self-awareness (see also Table 1).

**Table 2 tab2:** Elements of electronically delivered cognitive behavioral therapy for insomnia (eCBTi).

Session	Content
One	What is sleep? Provides an overview of the course and introduces the concepts of sleep, CBT, and insomnia.
Two	How various sleep habits impact on sleep. Provides stimulus control instructions, such as activities that are permitted or disallowed when in bed, daytime napping and what to do if sleep is not attained at night. Provides sleep restriction instructions, including setting specific bedtime, maintaining the same wake time, and restricting time spent in bed awake.
Three	Sleep hygiene education and discusses behavioral health practices, such as caffeine, alcohol, exercise, diet, smoking, and environmental factors’ impacts on sleep. Overview of relaxation techniques that support sleep.
Four	Role of automatic and negative thoughts and how they influence feelings. Identification of negative thoughts and alternative interpretations (cognitive restructuring)
Five	As session four; cognitive restructuring
Six	Review; summary of the main concepts of CBTi; what did I learn?

CBTi, cognitive behavioral therapy for insomnia.

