##### Coping strategies

2.5.1.5

To assess coping strategies, participants will be administered the short-form of the Stressverarbeitungsfragebogen 120 [Coping with stress questionnaire] (121). Favorable coping strategies are: Minimizing and trivializing, self-instructions, active problem solving. Unfavorable coping strategies are: Social withdrawal, catastrophizing, substance use. Higher summed scores reflect more pronounced favorable and unfavorable coping strategies.

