##### Emotion regulation

2.5.1.7

Participants will complete the Emotion Regulation Questionnaire (125), which focuses on cognitive reappraisal and emotion suppression. Item scores will be summed to create a total score; higher overall scores indicate more cognitive reappraisal and more emotion suppression.

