#### Intervention

2.8.1

ANOVAs for repeated measures are run with the factors Group (eCBTi vs. ACC), Time (baseline, week 3, week 6), and the Group x Time-interaction; dependent variables as reported in Table 2. Post-hoc analyses after Bonferroni-Holm are used for p-corrections for multiple testing. Single mean comparisons are performed with Cohen’s d effect sizes, as proposed by Becker (149). In case of missing values, such missing data will be replaced with the means or medians of the sample (144, 145, 150, 151). For the intervention study: Statistical procedures are run both by protocol (that is: only available data observed at any time point from every participant are considered) and by intent-to-treat (ITT) with the last intervention carried forward (LOCF) (152). Further, we consider the following confounders, that is to say, we statistically calculate, whether the pattern of results might get biased in the same or opposite directions for the following confounders: Age, gender, working condition, including current full time or part time positions as medical doctors, including their subspeciality such as neurosurgeon, anesthesiologist, or emergency MD, to name but a few, and military rank, or time lapse between the assessment and the last deployment.

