We expect that compared to individuals in the ACC, and compared to the baseline, at the end of the intervention, individuals in the eCBTi condition report improved sleep disturbances, including dysfunctional cognitions impairing sleep, along with improvements for symptoms of depression, anxiety, coping with stress, emotion regulation, concentration, social activity, strength and difficulties, and mental toughness, and with improvements for experiential avoidance and mindfulness self-awareness. The intervention study should also help to understand possible improvements in sleep disturbances and psychological well-being both in the professional/private and in the military context.

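### The emotion-regulation outcome is one total that adds reappraisal and suppression with the same sign, so it has no favourable direction and improvement cannot be read from it

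*Protocol article*

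**What the plan says.** Section 2.5.1.7 introduces the instrument with its two constructs: "Participants will complete the Emotion Regulation Questionnaire (125), which focuses on cognitive reappraisal and emotion suppression". The scoring rule follows at once: "Item scores will be summed to create a total score; higher overall scores indicate more cognitive reappraisal and more emotion suppression". The section mentions no separate score per strategy and no reverse scoring, and does not say which direction is favourable. No other part of the article adds any of these.

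The score is used in three places.

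- **Outcome status (section 2.5).** For the survey: "Secondary outcomes are psychological ill-being and well-being, including depression, anxiety, stress, coping strategies, emotion regulation, concentration". The intervention study takes over the same list, "including the dimensions metioned above, and additionally: Sleep-related cognitions, experiential avoidance, and mindfulness self-awareness".
- **Analysis (sections 2.8 and 2.8.1).** In the survey, emotion regulation is among the variables to be correlated with one another, insomnia included. Regressions then explore which psychological dimensions are most strongly related to insomnia. In the trial, "ANOVAs for repeated measures are run with the factors Group (eCBTi vs. ACC), Time (baseline, week 3, week 6), and the Group x Time-interaction".
- **Expectation (section 3.1.1).** Compared with control and with baseline, eCBTi participants should report better sleep, "along with improvements for symptoms of depression, anxiety, coping with stress, emotion regulation, concentration, social activity" and further dimensions.

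**The concern.** A hypothesis of improvement needs a score with a good end and a bad end. This total has neither. By the protocol's own description, its upper end means more of both strategies, and the protocol does not say whether more suppression is welcome.

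This matters in both studies. In the trial, a significant Group x Time interaction on the total could not be called improvement or deterioration without knowing which part moved. A null result could come from two real changes that offset each other. In the survey, the abstract sets out to separate dimensions associated with sleep disturbance from those that are not. A total whose parts relate to insomnia with opposite signs could be placed in the second group by construction.

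The scoring rule is stated outright, so this is not a detail left to a fuller document. An analyst who follows the article computes one number.

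**Working it through.** **The plan's own figure.** The article gives no effect size, SD or item count for this questionnaire, so there is no figure on this outcome to reproduce. The total sample size of 32 in section 2.7 can be reproduced (partial eta-squared 0.08, alpha 0.05, two groups, three measurements; power 0.955 at N = 32, assuming a correlation of 0.5 between repeated measures and sphericity). It has no bearing on this point.

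**Step 1: what the total measures.** Let R be the reappraisal part and S the suppression part. The rule gives T = R + S, so change in T = change in R + change in S.

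- R up 4 with S unchanged gives +4. R unchanged with S up 4 also gives +4.
- R up 5 with S down 5 gives 0. R down 5 with S up 5 also gives 0.

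Neither the size nor the sign of the change in T identifies what happened. This step needs no assumption about which strategy is beneficial.

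**Step 2: size of the distortion (illustration).** Assume each part has SD 1, weights w1 (R) and w2 (S) in the sum, correlation r between the parts, and standardised effects dR and dS. Then

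d(T) = (w1·dR + w2·dS) / √(w1² + w2² + 2·r·w1·w2).

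The effects, weights and correlations below are all assumed.

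| Scenario | Weights | r | d of total |
|---|---|---|---|
| Only R moves, dR = 0.5 | 1:1 | 0 | 0.5/√2 = 0.354 |
| Only R moves, dR = 0.5 | 1:1 | 0.3 | 0.5/√2.6 = 0.310 |
| Only R moves, dR = 0.5 | 1:1 | −0.3 | 0.5/√1.4 = 0.423 |
| dR = +0.5, dS = −0.5 | 1:1 | any | 0 |
| dR = +0.5, dS = −0.5 | 3:2 | 0 | (1.5 − 1.0)/√13 = 0.139 |
| dR = +0.5, dS = −0.5 | 3:2 | 0.3 | 0.5/√16.6 = 0.123 |
| dR = +0.5, dS = −0.5 | 3:2 | −0.3 | 0.5/√9.4 = 0.163 |
| dR = +0.3, dS = −0.5 | 1:1 | 0 | −0.2/√2 = −0.141 |

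If suppression stays still, its items only add variance: the effect shrinks and keeps its sign. If the two move in opposite directions, the offset is complete only when the changes are equal on the sum scale. Otherwise it is partial, and the sign follows the larger change.

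**Step 3: the survey (illustration).** Assume correlations with insomnia of −0.2 for R and +0.2 for S, with R and S uncorrelated. The total then correlates (w1·(−0.2) + w2·0.2)/√(w1² + w2²) with insomnia. This is 0 at equal weights and (−0.6 + 0.4)/√13 = −0.055 at 3:2. Two modest associations would be reported as almost none.

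**Why no power figures.** The planned test is a repeated-measures ANOVA. Power from a simple two-group comparison at 25 per arm would not describe it, and 25 is the number before drop-out.

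**The case against.** The strongest objection is that the protocol never calls suppression unfavourable. A reader might infer that benefit means more reappraisal and less suppression, and hence that a true benefit cancels to zero. The documents do not support that as a statement of fact. Section 2.5.1.7 gives neither strategy a direction. Table 2 assigns cognitive restructuring to sessions four and five, which makes a rise in reappraisal plausible, but no listed session targets suppression. The experiential-avoidance and mindfulness scales value acceptance, but they are different instruments. Full cancellation also needs equal and opposite changes. This objection limits the claim to possible offset or dilution. It does not rescue the score, because a predicted improvement still has no direction on it.

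A second objection is loose wording. Section 2.5.1.6 describes the three DASS-21 dimensions in one sentence, and the authors may intend two scores here as well. That is possible, but the emotion-regulation text orders a total, in the singular, and speaks of overall scores.

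A reader might also extend the point to coping in section 2.5.1.5: "Higher summed scores reflect more pronounced favorable and unfavorable coping strategies". That does not hold. The section sorts strategies into favourable and unfavourable and orders no combined total.

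Finally, this is one of many secondary outcomes. It is not named in the survey hypothesis in section 1.7 or among the abstract's expected trial results. That bears on its weight, not on whether it is right.

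**Conclusion.** The point holds in limited form. The prescribed total adds two distinct strategies with the same sign and has no favourable direction, so the improvement expected in section 3.1.1 can be neither confirmed nor refuted from it, and its correlation with insomnia in the survey is ambiguous. That conclusion follows from the text alone.

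The numerical size depends on assumptions the documents do not supply. If only reappraisal moves by 0.5 SD, the total shows about 0.35 at equal weights and zero correlation (0.31 to 0.42 for correlations of 0.3 to −0.3). If suppression moves oppositely by the same amount, the total shows 0 at equal weights and 0.12 to 0.16 at 3:2 weights over the same correlations. The scope is one secondary outcome of the trial and the survey correlations and regressions that use it. The primary sleep outcomes and the sample size are untouched. It should be corrected before the data are analysed, since a scoring choice made afterwards would be post hoc.

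**What to change.** In section 2.5.1.7, replace the total-score sentence with two separate scores, one for cognitive reappraisal and one for emotion suppression, and state the direction expected for each under eCBTi. In sections 2.5, 2.8, 2.8.1 and 3.1.1, treat them as two variables, and analyse and report each in both studies. Section 2.5.1.5 on coping needs no change for this reason.

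The same items are collected, so there is no added burden on participants. The cost is one additional secondary test in the Holm correction and one additional predictor in the survey regressions.

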##### Concentration

2.5.1.8

Participants complete the German version (Sadeghi-Bahmani and Brand, in preparation) of the Adult Concentration Inventory (126, 127); higher sum scores reflect more difficulties with concentration.

##### Social activity

2.5.1.9

Participants will complete the Social Adaptation Self-evaluation Scale [SASS; (128)]. Higher scores indicate higher social activity.

##### Strengths and difficulties

2.5.1.10

Participants will complete the Strength and Difficulties Questionnaire [SDQ; (129)] for adults. Dimensions are: Emotional problems, behavioral problems, hyperactivity, problems with peers and family members, and prosocial behavior.

##### Mental toughness

2.5.1.11

Participants complete the mental toughness short form [MTQ-18; (130, 136)], with higher scores reflecting a higher degree of mental toughness.

#### Measures for the eCBTi intervention and active control condition

2.5.2

The following questionnaires will be identical in both the initial survey and the intervention study: Sociodemographic and military-related information, sleep, physical activity, depression, coping strategies, depression, anxiety and stress, emotion regulation, social activity, strengths and difficulties, mental toughness (see Table 1).

In addition to the above mentioned questionnaires, the intervention study will also assess several additional psychological constructs with the following surveys:

##### Dysfunctional beliefs and attitudes about sleep

2.5.2.1

The Dysfunctional Beliefs and Attitudes about Sleep (DBAS; 16-items version) assesses cognitions and attitudes unfavorably impacting on sleep. Typical items are: “I need 8 h of sleep.,” or “It’s better taking sleeping pills.,” or “Sleep is unpredictable.” Answers are given on five-point Likert scales ranging from: 1 (= strongly disagree) to 5 (= strongly agree), with higher sum scores reflecting a more pronounced tendency to display dysfunctional beliefs and attitudes about sleep.

##### Pre-sleep cognitions and emotions, including bed time procrastination

2.5.2.2

The Bedtime Procrastination Scale [BPS (132, 133)] consists of nine items measuring subjective bedtime procrastination. Typical items are: “I easily get distracted by things when I actually would like to go to bed,” “I go to bed later than I had intended,” and “I want to go to bed on time but I just do not.” The response scale ranges from 1 (= almost never) to 5 (= almost always), with higher sum scores reflecting a higher tendency to delay to going to bed and to sleep.

##### Experiential avoidance

2.5.2.3

Participants will be administered the Experiential Avoidance Questionnaire [Hayes et al. (99, 137)]. It consists of 10 items, and typical items include: “I am afraid of my feelings.” or “My thoughts and feelings mess up my life.” Answers are given on 7-point Likert scales ranging from 1 (= never) to 7 (= always). Higher sum scores reflect a higher degree to accept also unpleasant experiences (emotions, cognitions), and accordingly, a lower degree of avoidance.

##### Mindfulness – self-awareness

2.5.2.4

Participants complete the Freiburg Mindfulness Inventory (FMI) (135). The short form consists of six items. Sample items are: “I perceive my feelings and emotions without having to react to them,” “I observe how my thoughts come and go,” “I accept unpleasant feelings,” and “I’m able to smile when I notice how I sometimes make life difficult.” Items are rated on a 4-point scale from 1 (= rarely) to 4 (= almost always), with higher sum scores reflecting a higher tendency of mindfulness and self-awareness.

### Interventions

2.6

#### eCBTi

2.6.1

We follow the standardized and validated intervention protocol for eCBTi (87, 91, 92; see Table 2). The intervention lasts for six consecutive weeks, with one session per week; a session lasts between 60 min to 70 min. Weekly homeworks need about 60–90′ per week.

#### Active control condition

2.6.2

As described extensively elsewhere (99, 138–141) participants in the control condition will meet once a week for six consecutive weeks for about 70 min. Thus, frequency, duration, and intensity are identical to the intervention condition. For homework, participants are asked to journaling. The control condition could not be considered as a *bona fide* intervention, given that the sessions exclude treatment elements that are truly intended to be therapeutic (142). Rather, participants will have group discussions on daily activities and daily problems. Participants are encouraged to exchange daily life experiences. The active control condition is not intended to be an active therapy, but to control for possible placebo effects in the intervention condition.

Licensed and trained clinical psychologists are responsible for both the eCBTi and the ACC.

### Sample size calculations

2.7

To calculate the sample size for the intervention study, we used the G*Power software (143). Based on previous studies on the efficacy of eCBTi (86–92), we expect a partial eta-squared of 0.08 (medium effect); alpha: 0.05; Power: 0.95; number of groups: 2; number of measurements: 3; total sample size: 32, that is, 16 per condition. To counterbalance possible drop-out, we assess 25 participants per condition.

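### For the stated partial eta-squared of 0.08, a total of 32 gives about 50% power, not 95%, because the within-person correlation is counted twice

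*Protocol article*

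**What the plan says.** Section 2.7 (Sample size calculations) is the only sample-size justification for the randomised comparison.

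- Tool: "we used the G*Power software (143"). Neither the module nor the effect-size option is named.
- Effect and error rates: "we expect a partial eta-squared of 0.08 (medium effect); alpha: 0.05; Power: 0.95".
- Origin of the effect: "Based on previous studies on the efficacy of eCBTi (86–92").
- Design and result: "number of groups: 2; number of measurements: 3; total sample size: 32, that is, 16 per condition".
- Enrolment: "To counterbalance possible drop-out, we assess 25 participants per condition". No dropout rate is given.

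Section 2.8.1 (Intervention) fixes the analysis as a repeated-measures ANOVA with Group, Time (three occasions) and their interaction. The abstract names condition-by-time interactions as the expected result, so the interaction is the test to be powered.

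**The concern.** A total of 32 is very small for 95% power at an effect labelled medium. The likely cause is a mismatch of effect-size scales. A partial eta-squared for a Group x Time effect is the effect sum of squares divided by the sum of the effect and within-person error sums of squares. Stable differences between people are already out of that denominator, so the benefit of correlated measurements is already in the number. G*Power's default repeated-measures option expects an f defined against the total variance within a cell, and it adds the benefit of the correlation itself. Putting the first kind of number into the second kind of formula counts the correlation twice.

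If so, the trial does not have the power it states. A non-significant interaction would be reported against a stated 95% power and could be read as evidence that eCBTi does not work, when the design had a large chance of missing the very effect it was planned for.

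**Working it through.** **Inputs from section 2.7:** partial eta-squared 0.08; alpha 0.05; target power 0.95; k = 2 groups; m = 3 measurements; N = 32 analysed; 50 enrolled.

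**Assumptions not in the document:** correlation rho between measurements (0.5, then varied) and sphericity epsilon = 1.

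**Step 1. Convert the effect.** f² = 0.08 / (1 − 0.08) = 0.08/0.92 = 0.0870, so f = 0.295.

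**Step 2. Reproduce the plan's figure.** In the default option, the noncentrality is lambda = f² × N × m / (1 − rho), with df1 = (k − 1)(m − 1) = 2 and df2 = (N − k)(m − 1).

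- N = 32, rho = 0.5: lambda = 0.0870 × 32 × 3 / 0.5 = 16.7, df 2 and 60, power 0.955.
- N = 30, rho = 0.5: power 0.941.

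So 32 is the first even total to reach 0.95. Under the same option, rho = 0 needs 62, rho = 0.3 needs 44 and rho = 0.7 needs 20. The printed 32 therefore depends on the 1/(1 − rho) factor with rho near 0.5.

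**Step 3. Power for a partial eta-squared as an ANOVA defines it.** There is no rho term. Two conventions are in use: lambda = f² × (N − 2) × 2, and lambda = f² × N × 2.

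| Total analysed | lambda | Power |
|---|---|---|
| 32 | 0.0870 × 60 = 5.2; 0.0870 × 64 = 5.6 | 0.50; 0.53 |
| 50 | 0.0870 × 96 = 8.3; 0.0870 × 100 = 8.7 | 0.72; 0.74 |

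Under the first convention, power of 0.80, 0.90 and 0.95 needs totals of 60, 78 and 94. Under the second, 0.80 needs 58 and 0.95 needs 92.

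A simulation of the mixed ANOVA, with a population partial eta-squared of 0.08 for the interaction, gave power of 0.53 at N = 32 for rho = 0.3, 0.5 and 0.7 alike. At N = 50 it gave about 0.75. The correlation makes no difference, as expected when it is already inside the effect size.

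**Step 4. What the stated calculation really assumes.** The ratio of noncentralities is 16.7/5.2 = 3.2 (or 16.7/5.6 = 3.0). Turned back into an ANOVA partial eta-squared, lambda = 16.7 is 16.7/(16.7 + 60) = 0.22, or 16.7/(16.7 + 64) = 0.21.

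**Step 5. A check that needs no correlation and no software option.** If 32 people show a partial eta-squared of exactly 0.08, then F(2,60) = 0.0870 × 60/2 = 2.61, p = 0.082. A design with 95% power would be clearly significant when it observes its own planning effect.

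**Step 6. Sensitivity.** With epsilon = 0.75 and the first convention, power is 0.43 at 32 and 0.63 at 50. With 50 analysed and epsilon = 1, the partial eta-squared detectable is about 0.094 at 80% power and about 0.14 at 95% power.

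**The case against.** The strongest reply is that 0.08 may have been meant on the software's own scale, as a planning value rather than a figure copied from published interaction tests. On that scale 32 gives 0.955 and 50 gives 0.997, and the paragraph would be right. The correlation, the module and the effect-size option are all unstated, and the cited studies are not available here. This cannot be excluded, but the text does not say it: the paragraph names a partial eta-squared and rests it on earlier eCBTi studies, and that term has a fixed meaning in the planned ANOVA.

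The label of medium does not settle the scale. Assume rho = 0.5, groups that diverge linearly and N = 32. The software-scale reading then implies a group difference of about 1.44 SD at week 6, since f² = d²/24 and d = √(24 × 0.0870). The ANOVA reading implies about 0.81 to 0.83 SD. Section 2.8 classes 0.80 and above as large, so neither fits the label, although the first is much further away.

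Three smaller points stand. The same 32 would come from the test of Time alone, which has the same noncentrality and degrees of freedom, so the match does not identify the module. The choice of noncentrality convention moves power by 2 to 3 percentage points, so ranges are proper. The example in Step 5 is the 50% power figure in another form and concerns 32 analysed; it illustrates the gap and is not separate evidence.

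The 25 per condition do not rescue the claim. The extra 18 people are there to cover dropout, and with none lost power is still only 0.72 to 0.74.

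**Conclusion.** The concern holds. For the effect size that section 2.7 names, power is 0.50 to 0.53 with 32 analysed, against the stated 0.95. It is 0.72 to 0.74 if all 50 are analysed. The stated power would need 92 to 94 analysed.

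The power figures rest on reading 0.08 as the partial eta-squared of the Group x Time test, and on sphericity; they do not depend on the correlation. The explanation of how 32 arose rests on an assumed correlation of 0.5 and the default option, which the exact match supports strongly. Nothing elsewhere in the article corrects the figure. Because the headline power is materially wrong for its own stated input, the paragraph should be corrected.

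**What to change.** Keep 25 per condition and rewrite section 2.7:

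1. Say that for a partial eta-squared of 0.08 as an ANOVA reports it, with alpha 0.05 and three measurements, power is about 0.72 with 50 analysed and about 0.50 with 32. Alternatively, say that 50 analysed give 80% power for 0.094 and 95% power for 0.14.
2. State the effect-size scale, the assumed correlation and epsilon used in the calculation.
3. Delete the claim of 95% power with 16 per condition. If 0.08 was truly meant on the software's own scale, say so, give the equivalent ANOVA value (about 0.21 to 0.22 at rho = 0.5) and justify an effect of that size.

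The cost is one reworded paragraph and a less favourable power statement. Enrolment and analysis do not change. Restoring 95% power for 0.08 would need 92 to 94 analysed before any allowance for dropout, but the correction does not require that.
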